#### Secondary outcomes

##### CSKO score

The Chinese Scale for Knee Osteoarthritis (CSKO) score was performed for each follow-up [22], with the calculation of the total score of CSKO being compared before and after treatment.

### X-ray data acquisition

Taking X-ray of the double knee joint with weight loading is at the adem position. The Kellgren and Lawrence classification criteria will be used on AP film to evaluate the degree of degeneration and the width of medial and lateral tibiofemoral joint space [17]. At the end of treatment, the X-ray of the double knee joint was taken again. Compare the width changes of medial and lateral tibiofemoral joint space on standard load positive X-ray before and after treatment.

### MRI data acquisition

Using Siemens 3.0T MRI to obtain the patient’s knee T2 mapping sequence. Using the Recht criteria to evaluate cartilage degeneration [23]. Measure the average thickness and volume of cartilage at the same time.

After the end of treatment, MRI images were taken of the affected limb for the MRI score of cartilage defect.

### Safety outcomes

(1) Vital signs: body temperature, resting heart rate, respiratory, and blood pressure after 10 min of rest (systolic blood pressure, diastolic blood pressure). (2) Laboratory examination: blood routine (RBC, WBC, platelet, hemoglobin), urine routines (urine red cell, LEU, urinary protein, glycated hemoglobin alc), stool routine+occult blood, and liver function (ALT, AST), and renal function (BUN, Cr, 12 lead routine electrocardiogram). (3) Manipulation-related adverse events, such as ecchymosis, subcutaneous hemorrhage, fracture, and dislocation. (4) Drug-related adverse events, such as gastrointestinal tract response. (5) Other adverse events.

The safety of each therapy was evaluated by comparing the changes in blood and urine routine, liver and kidney function, electrocardiography before and after the treatment, and the incidence of adverse events during the treatment.

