## Methods and design

The main purpose of this study is to compare the safety and efficacy of evidence-based traditional Chinese medicine massage and External Diclofenac Diethylamine Emulgel in KOA patients. Three hundred participants will be recruited for the study. Clinical data measurements, X-rays, and MRI scans will be evaluated at baseline and the end of treatment (Fig. 1). The study has been approved by the ethical committees of Guang’anmen Hospital (NO:201-135-KY-1) and registered in the Chinese Clinical Trial Registry (http://www.chictr.org.cn/showproj.aspx?proj=24457). The registration number is ChiCTR1800014400. The protocol will be reported following Standard Protocol Items: Recommendations for Interventional Trials (SPIRIT) statement.

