### Statistical analysis

All statistical analyses will be performed with the SPSS software (SPSS 20.0, SPSS Inc., Chicago, IL, USA) by statisticians who are independent of the research team and blinded to the group allocation. Data analysis will be based on the intention-to-treat (ITT) principles. All numerical data will be presented as the mean ± SD, and categorical variables will be described with percentages (%). All the statistical tests are bilateral inspection; *p* < 0.05 is considered statistically significant. Paired *t* test or the paired rank sum test is used for the comparison within the groups; the *χ*^2^ test or Fisher’s exact probability method is used for the count data, and the Wilcoxon rank sum test is used for the rank data between groups. CMH *χ*^2^ test is used for the primary outcome of WOMAC improve rate. It is necessary to adjust the baseline and centers of the changes in WOMAC score between the groups with the covariance method.

The secondary outcome includes CSKO score, X-ray data, and MRI data, which are all measurement data, and a group *t*-test or the Wilcoxon rank-sum test is used for comparison between the groups. The *χ*^2^ test or Fisher’s exact probability method is used for participants’ dropout and adverse events rate analysis.

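### Laboratory and ECG safety is described as before-after change for each therapy, and no between-arm analysis is assigned to numeric laboratory or vital-sign values, although comparing safety is a main purpose

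*Protocol article*

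**What the plan says.** Protocol article, Methods and design: the main purpose is to "compare the safety and efficacy of evidence-based traditional Chinese medicine massage and External Diclofenac Diethylamine Emulgel in KOA patients".

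Protocol article, Safety outcomes: vital signs, blood, urine and stool tests, liver and kidney function and an ECG are listed, together with adverse events. The evaluation rule is "The safety of each therapy was evaluated by comparing the changes in blood and urine routine", then liver and kidney function, and "electrocardiography before and after the treatment, and the incidence of adverse events during the treatment". Vital signs are listed as a safety outcome but do not appear in this rule.

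Protocol article, Statistical analysis: all tests are two-sided at 0.05. A paired t test or "the paired rank sum test is used for the comparison within the groups". Between-group methods are then assigned by endpoint:
- WOMAC: CMH test for the improvement rate, and covariance adjustment for baseline and center for the change.
- CSKO, X-ray and MRI: group t-test or Wilcoxon rank-sum test.
- Dropout and adverse events: chi-square, or Fisher's "exact probability method is used for participants’ dropout and adverse events rate analysis".

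Two general lines are tied to no endpoint: chi-square or Fisher for count data, and "the Wilcoxon rank sum test is used for the rank data between groups". Numeric laboratory and vital-sign values appear in none of the endpoint-specific assignments.

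**The concern.** The purpose is comparative, but the stated rule for laboratory and ECG results takes each therapy as its unit and before versus after as its contrast. For a numeric value such as ALT, creatinine or hemoglobin, the stated method that most directly fits that rule is the paired within-group test.

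A paired test within an arm does not answer a comparative question. It mixes any effect of treatment with whatever would have changed over ten weeks anyway, including regression to the mean. Its result also depends on the size of the arm, and the arms here are planned at 200 and 100. Two arms with the same true change can therefore give different verdicts. Two arms with different true changes can both be significant and look alike. If the safety conclusion were drawn from such results, a difference could be reported where none exists, or a real one overlooked.

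**Working it through.** **Plan's own figure.** The article gives no power or precision figure for safety. Its one calculated sample size, 85.49 per group, concerns efficacy rates. It reproduces as [0.956 × 0.044 + 0.798 × 0.202] × 10.5 / 0.158² = 0.20326 × 10.5 / 0.024964 = 85.49, where 10.5 is the rounded factor for two-sided 0.05 and 90% power (the power is not stated and is assumed here). It does not bear on this point.

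**Step 1: which methods are tied to which data.**

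| Data | Between-group method stated |
|---|---|
| WOMAC | CMH; covariance adjustment |
| CSKO, X-ray, MRI | group t-test or Wilcoxon |
| Dropout, adverse event rates | chi-square or Fisher |
| Laboratory or ECG results, if put in categories | none assigned; general count or rank lines could apply |
| Numeric laboratory and vital-sign values | none assigned |

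**Step 2: what follows if paired tests are used for the last row.**

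Inputs from the article: n = 200 and n = 100 (Sample size); two-sided 0.05 (Statistical analysis). Assumption: the same true mean change e in both arms, in units of the SD of the change. The article gives no laboratory means or SDs, so a range is shown.

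Chance that an arm of size n is significant, by normal approximation:

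P(n) = Φ(e√n − 1.96) + Φ(−e√n − 1.96)

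Chance that exactly one arm is significant (the arms are independent):

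D = P(200)[1 − P(100)] + P(100)[1 − P(200)]

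Example at e = 0.20: e√n is 2.83 and 2.00, so P(200) = 0.807 and P(100) = 0.516. D = 0.807 × 0.484 + 0.516 × 0.193 = 0.49.

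| e (SD of change) | P(200) | P(100) | exactly one arm significant |
|---|---|---|---|
| 0 | 0.050 | 0.050 | 9.5% |
| 0.05 | 0.109 | 0.079 | 17% |
| 0.10 | 0.293 | 0.170 | 36% |
| 0.15 | 0.564 | 0.323 | 52% |
| 0.20 | 0.807 | 0.516 | 49% |
| 0.25 | 0.942 | 0.705 | 32% |
| 0.30 | 0.989 | 0.851 | 16% |
| 0.40 | 1.000 | 0.979 | 2% |

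The noncentral t gives nearly the same results; at 0.20 SD the powers are 0.804 and 0.508, with 49% discordant.

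**Step 3: how much is due to 2:1 allocation.** With 150 per arm, D = 2P(150)[1 − P(150)], which gives 9.5% at 0, 36% at 0.10, 50% at 0.15 and 43% at 0.20 SD. Most of the problem lies in judging each arm separately. Unequal allocation adds little at small shifts and somewhat more from about 0.20 SD upward. It also makes the discordance lopsided: at 0.20 SD, massage alone is significant in 39% and gel alone in 10%.

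**Step 4: the direct comparison.** A between-arm test of the changes is falsely positive 5% of the time whatever the common shift. For a true difference of 0.35 SD its power is Φ(0.35/√(1/200 + 1/100) − 1.96) = Φ(2.858 − 1.960) = 0.82, without counting any gain from baseline adjustment.

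**The case against.** The strongest reply is that the article does not confine safety to within-arm tests.

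- The rule's verb also governs the incidence of adverse events during treatment. That has no before value, so the comparison there must be between therapies, and chi-square or Fisher is named for it. The same verb could be read that way for laboratory changes.
- The outcome sections for WOMAC, CSKO and X-ray also speak of comparison before and after treatment, and the statistical section then gives each a between-group test. The phrase may only define the change variable.
- The general count and rank lines could serve ECG, occult blood, urine findings or any laboratory result classed as abnormal.
- An article may leave the choice of test for a laboratory value to the full protocol.

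The first three points stand. A reader might infer that laboratory and ECG safety is judged only within arms and that the arms are never compared; the text does not support that. Nor does any passage say that within-arm p-values decide safety. The link from the safety rule to the paired tests is an inference.

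The fourth point does not dispose of the matter. An unnamed test alone would be no finding, but the article states a rule, by therapy and before versus after, that does not by itself serve its comparative purpose. The WOMAC, CSKO and X-ray parallel also works the other way: for those endpoints the between-group step is written down, and for numeric laboratory and vital-sign values it is not.

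A reader might also take the eight named blood tests (RBC, WBC, platelets, hemoglobin, ALT, AST, BUN, Cr) and calculate 1 − 0.905⁸ = 55% of trials with at least one discordant parameter when nothing changes, and blame the 2:1 ratio. That is not supported. The 9.5% per parameter is the same under any allocation. Independence is doubtful for pairs such as ALT and AST. Eight between-arm tests at 5% would, on the same assumption, give at least one false positive in 1 − 0.95⁸ = 34%.

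**Conclusion.** The point holds in a limited form. The article describes laboratory and ECG safety as before-after change for each therapy. It assigns no between-arm analysis to numeric laboratory or vital-sign values, although it makes comparing the safety of the two treatments a main purpose. Adverse event rates are compared between arms, and categorised laboratory or ECG results could be.

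The numerical consequence is conditional on the paired tests being used for these values and their verdicts being set against each other. Its size depends on the unknown shift: it peaks around 0.15 to 0.20 SD and is negligible for large shifts, so no single figure should be quoted as the expected error rate. The unequal allocation aggravates the problem at moderate shifts but is not its main cause.

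**What to change.** In Safety outcomes and Statistical analysis, state that:

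1. changes in numeric laboratory and vital-sign values to the end of treatment are compared between arms, adjusted for baseline (analysis of covariance), and reported as a difference with 95% CI;
2. newly abnormal results, including ECG, are compared between arms as proportions, with a risk difference and 95% CI;
3. within-arm changes are descriptive only, and no conclusion about a difference between treatments is drawn from within-arm p-values.

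The cost is a few sentences and a few more table columns. No new data, visits or patients are needed.

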### Data management and monitoring

The outcome assessors will use the CRFs to collect the data which consists of treatment effects, adverse events, and safety evaluations. Then, two data administrators who do not belong to the research team and are blinded to group allocation will independently receive the completed CRF and enter it into the Excel database (Microsoft, Redmond, WA, USA). They must complete rigorous data monitoring training. Then, they enter the real-time data into the China Clinical Trial Registry (http://www.chictr.org.cn), where the electronic data management system will be used for real-time tracking and monitoring of test data from the Research Office of Guang’anmen Hospital.

### Statistical analysis

All statistical analyses will be performed with the SPSS software (SPSS 20.0, SPSS Inc., Chicago, IL, USA) by statisticians who are independent of the research team and blinded to the group allocation. Data analysis will be based on the intention-to-treat (ITT) principles. All numerical data will be presented as the mean ± SD, and categorical variables will be described with percentages (%). All the statistical tests are bilateral inspection; *p* < 0.05 is considered statistically significant. Paired *t* test or the paired rank sum test is used for the comparison within the groups; the *χ*^2^ test or Fisher’s exact probability method is used for the count data, and the Wilcoxon rank sum test is used for the rank data between groups. CMH *χ*^2^ test is used for the primary outcome of WOMAC improve rate. It is necessary to adjust the baseline and centers of the changes in WOMAC score between the groups with the covariance method.

The secondary outcome includes CSKO score, X-ray data, and MRI data, which are all measurement data, and a group *t*-test or the Wilcoxon rank-sum test is used for comparison between the groups. The *χ*^2^ test or Fisher’s exact probability method is used for participants’ dropout and adverse events rate analysis.

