**Methods and design:**

A randomized controlled trial in which 300 participants diagnosed with KOA will be recruited and randomly allocated to either the experimental group or the control group in a ratio of 2:1. Two hundred participants will receive evidence-based traditional Chinese medicine massage 2 sessions per week for 10 weeks as the experimental group, and 100 participants will receive External Diclofenac Diethylamine Emulgel 3–4 times per day for 10 weeks as the control group. The patients in the two groups will receive follow-up at two time points at 5 weeks and 10 weeks from the beginning of treatment, respectively. The MRI scans and X-ray will be performed at baseline and at the end of the intervention. The primary outcome will be the changes in the Western Ontario and McMaster Osteoarthritis Index (WOMAC). Secondary outcomes will be measured by the PRO scale for knee osteoarthritis based on the concept of traditional Chinese medicine (Chinese scale for knee osteoarthritis (CSKO)), X-ray evaluation, and MRI scan evaluation. The data of WOMAC and CSKO will be analyzed at the baseline, 5 weeks, and 10 weeks from the beginning of treatment. The data from MRI scans and X-rays will be analyzed at baseline and at the end of the intervention. The significance level sets as 5%. The safety of interventions will be evaluated after each treatment session.

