In order to provide clinicians a complementary and alternative therapy for patients with KOA, and to determine whether evidence-based traditional Chinese medicine massage is a safe and effective therapy, we design and conduct the trial. Compared to topical NSAIDs (e.g., Diclofenac Emugel), which is strongly recommended (level 1a), massage is conditionally (level 3) recommended by the OARSI guidelines [6]. In the trial, we hypothesized that the evidence-based traditional Chinese medicine massage group would be non-inferior to the External Diclofenac Diethylamine Emulgel group in the treatment for KOA. In order to enhance the reliability of evidence-based traditional Chinese medicine massage in the treatment of KOA, we take the External Diclofenac Diethylamine Emulgel as the control group to evaluate the efficacy and safety in the study. In the overall design of the experiment, this scheme has randomization, control, and multi-center clinical trial.

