### Sample size

According to the literature, the average effective rate of treating knee osteoarthritis only through massage is 95.6% and 79.8% by application of external diclofenac diethylamine emulsion latex [15]. According to the sample size calculation formula, the minimum sample size of each group is *n* = 85.49. Considering expulsion case and getting significant results, at the same time, in order to implement layered research in the experimental group, we planned the ratio of the cases in the experimental group and the control group is 2:1, and the number of included cases was 300. There were 200 cases in the experimental group, and 100 cases were in the control group.

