#### Control group

One hundred patients in the control group will receive External Diclofenac Diethylamine Emulgel (Beijing Novartis Pharma Ltd. producing, trade name: Vitalin Emulgel) treatment (3–4 times per day for 10 weeks). Other interventions will be similar to the experimental group.

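### The hypothesis is non-inferiority but ITT is the only analysis basis named; a pre-specified per-protocol analysis beside it would be a cheap safeguard

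*Protocol article*

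**What the plan says.** The Introduction of the protocol article gives the hypothesis: the massage group "would be non-inferior to the External Diclofenac Diethylamine Emulgel group in the treatment for KOA". The Statistical analysis section sets the basis of analysis: "Data analysis will be based on the intention-to-treat (ITT) principles". No per-protocol or other supportive set is named in the article.

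Four other statements bear on the point.

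- **Treatment delivery.** Massage is given as 20 sessions over 10 weeks (Experimental group). The comparator is a gel applied 3–4 times a day for 10 weeks: "One hundred patients in the control group will receive External Diclofenac Diethylamine Emulgel" (Control group).
- **Rescue drug.** Both arms appear to have the same oral rescue medication. The Experimental group section describes it, and the Control group section says that other interventions are similar.
- **Compliance.** Dropout criteria lets researchers remove poorly compliant patients and counts them as dropouts. Trial conduct requires records of drug receipt, distribution and return. No analysis in the Statistical analysis section uses compliance.
- **Tests.** "All the statistical tests are bilateral inspection", at p < 0.05, with a CMH chi-square test for the WOMAC improvement rate. No margin and no confidence-interval rule are stated.

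**The concern.** In a superiority trial, ITT is the cautious choice: patients who do not take their treatment usually weaken the contrast and make a difference harder to show. In a non-inferiority trial, anything that makes the arms more alike helps the claim. If massage were truly worse than gel used as intended, under-use of the gel, or under-use in both arms with the same rescue drug to fall back on, could hide that disadvantage.

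Under-use is plausible here. The gel has to be applied several times a day for 10 weeks, and participants know which treatment they have. With ITT as the only analysis of the primary comparison, a non-inferiority result could reflect poor adherence, and no planned efficacy analysis would separate the two explanations. Adding a margin and a confidence interval, which the plan also needs, would not by itself remove this.

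**Working it through.** **1. The plan's own figure.** Sample size gives these rates: "the average effective rate of treating knee osteoarthritis only through massage is 95.6% and 79.8% by application of external diclofenac diethylamine emulsion latex", and concludes "the minimum sample size of each group is *n* = 85.49". The unpooled two-proportion formula for a difference, two-sided 5%, reproduces it if 90% power is assumed (power is not stated) and (1.96 + 1.28)² is rounded to 10.5:

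n = 10.5 × [0.956 × 0.044 + 0.798 × 0.202] / (0.956 − 0.798)² = 10.5 × 0.20326 / 0.024964 = 85.49.

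With unrounded normal quantiles it is 85.55. No margin is needed to reach the figure, so the article supplies none that could be used below.

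**2. Set-up of the illustration.**

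- From the article: gel response 79.8%, 200 massage and 100 gel patients.
- Assumed: margin M of 10 or 15 points; one-sided 2.5%; massage truly worse by exactly M when treatment is taken as assigned; a fraction f of non-adherers who respond at rate r, with r between 30% and 79.8%.

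Observed rate in an arm: p′ = (1 − f)p + f·r.

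SE = √[p′gel(1 − p′gel)/100 + p′mas(1 − p′mas)/200].

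False-claim rate = Φ[(p′mas − p′gel + M)/SE − 1.96]. At f = 0 this is 2.5%.

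**3. Non-adherence in both arms.** Worked case with M = 10 points, f = 20%, r = 30%:

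- gel: 0.8 × 0.798 + 0.2 × 0.30 = 0.6984
- massage: 0.8 × 0.698 + 0.2 × 0.30 = 0.6184
- difference −0.080; SE = √(0.002106 + 0.001180) = 0.0573
- Φ(0.020/0.0573 − 1.96) = Φ(−1.61) = 5.4%

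Over the range of r:

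| Non-adherence in both arms | Margin 10 points | Margin 15 points |
|---|---|---|
| 10% | 3.8–3.9% | 4.6–4.7% |
| 20% | 5.4–5.8% | 7.5–8.3% |
| 30% | 7.3–8.5% | 11.5–13.8% |

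**4. Non-adherence of 20% in one arm only.**

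| Arm affected | Non-adherers' response | Margin 10 points | Margin 15 points |
|---|---|---|---|
| Gel | 30% | 42.5% | 41.6% |
| Gel | 79.8% (same as adherent gel users) | 2.5% | 2.5% |
| Massage | 30% | 0.03% | 0.05% |
| Massage | 79.8% (same as adherent gel users) | 5.8% | 8.3% |

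Direction and size depend on which arm under-adheres and how those patients fare.

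**5. WOMAC change, as a second illustration.** Assume a margin of 5 points, an SD of 15 and a true difference that shrinks by a fraction q. All three are assumptions. SE = 15 × √(1/200 + 1/100) = 1.837. The false-claim rate is 1 − Φ(1.96 − q × 5/1.837), which gives 4.6%, 7.8% and 12.6% for q = 10%, 20% and 30%.

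**6. If the planning rates are right.** Massage is then 15.8 points better. Equal dilution of 20% leaves 0.8 × 15.8 = 12.6 points, which works against massage. The inflation in steps 3 to 5 arises only where massage is truly worse, which is the case that a non-inferiority test must guard against.

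**The case against.** The strongest objection is that this is a condensed article. Analysis sets are commonly defined in a full protocol or SAP, and the full protocol is said to be available on request. A reader might infer from the ITT sentence that a per-protocol analysis is excluded; the article does not say so. What stands against the objection is that the article is not silent: it names ITT as the basis of analysis beside a non-inferiority hypothesis, and that pairing can be commented on. If a per-protocol set exists elsewhere, one sentence settles the matter.

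A second objection is that the plan contains no non-inferiority test whose error could be inflated. This is correct. The sizing and the tests are for a difference, and for those tests ITT is the usual cautious choice. The mismatch between the hypothesis and the tests is the larger problem, and the present point has force only once that is repaired.

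Three stronger readings are tempting and are not supported.

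- *Poor adherence in either arm favours the claim.* Step 4 shows that massage-only non-adherence with poor outcomes makes non-inferiority much harder to claim.
- *Nothing in the plan would reveal poor adherence.* Drug return records are kept, poor compliance is a listed reason for removal, and dropout is compared between arms. What is missing is an efficacy analysis that uses this information.
- *Non-inferiority must be rejected unless both sets meet the margin.* Participants and therapists are unblinded, so adherence may depend on arm and response, and a per-protocol estimate can be biased either way. A rigid dual criterion goes further than the document's faults justify.

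It is also unclear whether patients removed for poor compliance would have week-10 data. How far they would dilute the ITT comparison is therefore assumed.

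**Conclusion.** The point holds as a cheap improvement; it is not a demonstrated error in a planned test. With a non-inferiority hypothesis, ITT alone is not reliably conservative: non-adherence in the gel arm, or in both arms, can pull the arms together, while non-adherence in the massage arm alone can push them apart.

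The size cannot be derived from the article. Under assumed margins of 10 to 15 points and 20% non-adherence in both arms, a nominal 2.5% false-claim rate becomes about 5% to 8%. The figures near 42% for gel-only non-adherence rest on non-adherers responding at 30%, and should be read as an unfavourable case. The margins, adherence levels, non-adherers' response and, for WOMAC change, the SD are all assumptions.

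Every figure measures error against the difference when treatment is taken as assigned. If the trial wants only the difference under actual use, ITT addresses that directly and the per-protocol result is supplementary.

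**What to change.** Make the change together with a stated non-inferiority margin and a confidence-interval test; without those it has nothing to act on.

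1. Keep ITT as the main analysis.
2. Add a pre-specified per-protocol analysis of the primary comparison.
3. Define the set before any data are split by arm, from sessions attended, gel dispensing and return records, and use of prohibited treatment. Do not define it from investigator removals, which unblinded judgement can influence. The return check under Trial conduct is worded for tablets, so state that it covers the gel.
4. Report both analyses against the same margin. Treat a non-inferiority conclusion as robust only if they are consistent, and explain any disagreement.

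The cost is a few sentences and one extra analysis; session counts and drug records should already be to hand. The claim becomes slightly harder to make. The per-protocol set is not fully protected by randomisation, so it supports the ITT result and does not replace it.
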